# ACEMg-mediated hearing preservation in cochlear implant patients receiving different electrode lengths (PROHEARING): study protocol for a randomized controlled trial

**DOI:** 10.1186/s13063-016-1526-7

**Published:** 2016-08-08

**Keywords:** Cochlear implant, Antioxidants, Free radicals, Hearing preservation, Residual hearing, EAS, Electric acoustic stimulation

## Abstract

**Background:**

The indications for a cochlear implant (CI) have been extended to include patients with some residual hearing. Shorter and thinner atraumatic electrodes have been designed to preserve the residual hearing in the implanted ear. However, the insertion of the electrode array into the cochlea, with potential mechanical trauma and the presence of this foreign body inside the cochlea, may lead to free radical formation and reduced blood perfusion of the cochlea which can result in the loss of residual hearing.

**Methods/design:**

In this single-center, randomized, placebo-controlled, double-blind phase II clinical trial the effect of free radical scavengers and a vasodilator on the residual hearing of 140 CI patients will be evaluated. The formulation is composed of β-carotene (vitamin A), ascorbic acid (vitamin C), dl-α-tocopherol acetate (vitamin E) and the vasodilator magnesium (Mg), or ACEMg. Medication is administered twice daily per os for approximately 3 months. The primary measure is based upon the reduction in postoperative low-frequency air-conducted pure-tone thresholds compared to preoperative thresholds in ACEMg-treated patients compared to those of a placebo group. Additionally, the effect of different electrode lengths (20, 24 and 28 mm) is analyzed. Study visits are scheduled 2 days before surgery, at first fitting, which is the adjustment and start of stimulation via CI 4 weeks after surgery and 3, 6, 9 and 12 months after first fitting. The primary endpoint is the air-conduction hearing loss at 500 Hz 3 months after first fitting. Additionally, speech recognition tests, hearing aid benefit in the implanted ear and electrophysiological measurements of implant function are assessed.

Since this is a blinded clinical trial and recruitment is still ongoing, data continue to accrue and we cannot yet analyze the outcome of the ACEMg treatment.

**Discussion:**

There is an unfulfilled need for new strategies to preserve acoustic hearing in CI patients. This study will provide first-in-man data on ACEMg-mediated protection of residual hearing in CI patients. Performing all surgeries and patient follow-up at one study site improves consistency in diagnosis and therapy and less variability in surgery, audiological test techniques and fitting. This approach will allow investigation of the influence of ACEMg on residual hearing in CI patients.

**Trial registration:**

The German Bundesinstitut für Arzneimittel und Medizinprodukte (BfArM) application number 4039192, was registered on 6 December 2013 with protocol amendment version 3.0 from 19 August 2014. EudraCT number: 2012-005002-22.

## Background

The cochlear implant (CI) is the standard treatment for unilateral and bilateral severe/profound hearing loss, both in adults and children. The CI stimulates the auditory nerve electrically through electrodes placed inside the inner ear, the cochlea. Recently, as speech understanding with the CI has improved, indication criteria have been extended towards patients with more residual hearing. At the same time, thinner and shorter atraumatic electrodes have been designed to preserve the (low-frequency) residual hearing in the implanted ear [1, 2]. If hearing has been preserved, then the electrical stimulation of the implant may be combined with a hearing aid in the same ear (electric acoustic stimulation, EAS).

The insertion of the electrode array into the cochlea with potential mechanical trauma, and the chronic presence of this foreign body inside the cochlea may induce loss of residual hearing. As Talbot and colleagues stated in 2004, a substantial acoustic hearing loss occurs in 24 % of EAS CI patients, and among them 13 % show a total loss of residual hearing [3]. More recent studies prove that the occurring problem is not yet solved since a large number of patients continue to suffer from partial or total loss of residual hearing. In 15 % of patients analyzed by Skarzynski a partial to total hearing loss was observed [4]. Other studies published a complete loss of residual hearing in 22.7 % of subjects and a partial loss of hearing in 50.1 % of the total patient population (*n* = 22) [5] or a mean threshold shift >15 dB 24 months after first fitting (FF) in 41.2 % (Cochlear Implant Model Hybrid-L24, *n* = 51) and 71.4 % (Cochlear Implant Model CI422, *n* = 28), respectively [6].

Experimental studies on the auditory system have demonstrated that antioxidants plus a vasodilator reduce both noise- and drug- (aminoglycoside)-induced inner ear pathology and hearing loss by over 75 % [7]. This formulation is β-carotene (converted in the body to vitamin A), ascorbic acid (vitamin C), dl-α-tocopherol acetate (vitamin E) and the vasodilator magnesium. Together (ACEMg) they are remarkably effective in vivo. Data indicate that free radicals play a key role in sensory and neural cell death and loss of residual hearing with CI implantation [8, 9] which reduces the benefits of implantation. The goal of ACEMg treatment is to eliminate one important contributing factor, the stress of surgery and implantation of a foreign body that may reduce residual acoustic hearing in the implanted patient.

Our PROHEARING clinical trial (PROtect residual HEARING) is the first human trial to assess the efficacy of ACEMg to prevent permanent hearing loss in CI patients with residual hearing.

## Methods/design

The PROHEARING trial is conducted in accordance with the Declaration of Helsinki and complies with the principles of Good Clinical Practice (GCP) and Good Manufacturing Practice (GMP). The protocol is approved by the Independent Ethics Committee (IEC) of Hannover Medical School (MHH) and by the national legal authority, the Bundesinstitut für Arzneimittel und Medizinprodukte (BfArM).

The trial is registered on the European Clinical Trials Database (EudraCT Number: 2012-005002-22). It is funded by a grant from the European Commission 7th Framework Program in Public Health research. The trial is being coordinated by the Clinic of Otorhinolaryngology of MHH (sponsor). The MHH Institutes for Biostatistics and for Clinical Pharmacology support the trial with their expertise and the Hannover Clinical Trial Center (HCTC) is the management center of the study and responsible for clinical monitoring and data management. The trial complies with the principles of GCP and is carried out in accordance with applicable legislation and the Standard Operating Procedures of MHH.

The PROHEARING trial is a single-center, randomized, placebo-controlled, double-blind, phase II trial including adults admitted to the MHH Department of Otorhinolaryngology who are suffering from hearing loss, have a defined level of residual hearing and receiving a cochlea implant.

The study has the primary objective to demonstrate that ACEMg is more efficacious than placebo in preserving residual hearing during cochlear implantation by comparing the hearing loss 3 months after FF at 500 Hz in air-conducted pure-tone audiometry.

Key secondary objectives are:To investigate the drug effect over time (hearing loss in ACEMg compared to placebo at 500 Hz 6, 9 and 12 months after FF)To compare ACEMg and placebo for hearing loss at different frequencies of pure-tone audiometry (125, 250 and 750 Hz, 1, 1.5, 2, 3, 4, 6 and 8 kHz) over time (months 3, 6, 9 and 12 after FF)To compare efficacy by means of speech perception, functional hearing and impedancesTo evaluate the effect of electrode length on hearing loss

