### Clinical outcome measures

The primary outcome of the PROHEARING trial will be the hearing loss at the implanted ear at 500 Hz 3 months post FF (hearing loss = 3 month post-FF threshold minus 1–2 days preoperative threshold) measured by air-conducted pure-tone audiometry. Additionally, secondary endpoints are:Hearing loss at the implanted ear measured by pure-tone audiometry at 500 Hz 6, 9 and 12 months post FFHearing loss measured by pure-tone audiometry for other frequencies (125 and 250 Hz, 1, 2 and 8 kHz) over time (months 3, 6, 9 and 12 post FF)Speech perception by the Oldenburger Satztest (OLSA), month 12Functional Hearing questionnaire NCIQ, months 3 and 12 after FFImpedances (Ω) at all timepointsOccurrence of tinnitus: Tinnitus Questionnaire at all timepoints

Safety endpoints:All serious adverse events (SAEs)All adverse events (AEs) leading to discontinuation of IMP intake

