### Statistical analysis

The primary analysis is based on the intention-to-treat (ITT) population consisting of all randomized patients who took the study medication at least once. The primary null hypothesis of equal hearing loss in ACEMg and placebo will be evaluated with an analysis of covariance (ANCOVA) model including the factor treatment (ACEMg versus placebo), the baseline residual hearing, surgeon, planned length of electrode and formulation of medication (chewing pills versus softgel capsules). The null hypothesis, of no smaller reduction in residual hearing for ACEMg patients, is rejected if the upper bound of the ANCOVA-derived two-sided 95 % confidence interval of the difference in change from baseline (ACEMg minus placebo) is less than 0.

To evaluate the robustness of the estimated treatment effect, the primary analysis will be repeated based on the per-protocol population. In addition, the primary objective is evaluated with the nonparametric, stratified Gehan test as a sensitivity analysis. Moreover, analysis will be conducted using real length of electrode instead of planned length of electrode as independent factor.

Secondary analyses will be conducted on the ITT population and on the per-protocol population as sensitivity analyses. Key secondary analyses include the comparison of ACEMg group to placebo in terms of residual hearing for different frequencies and different timepoints after surgery. All analyses will be performed in line with the primary analysis using ANCOVA. Differences in the treatment effects within patient groups with different electrode length are evaluated descriptively.

Absolute and relative frequencies of (serious) adverse events will be listed for each treatment group separately. Differences will be analyzed in a descriptive manner. The safety population will be used for analysis.

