### Data handling conventions and missing values

The primary endpoint is residual hearing measured in decibels for a frequency of 500 Hz by air-conducted pure-tone audiometry at the implanted ear. If the patient reaches the upper detection limit of the 500-Hz air-conducted pure-tone audiometry of 110 dB without hearing, the measurement is set to 120 dB as the upper limit of detection + 10 dB. This “upper limit +10” approach is used in all analyses concerning residual hearing (for all frequencies).

The anticipated drop-out rate is expected to be low in PROHEARING as patients in the initial phase after CI are closely followed for clinical reasons. Frequency and reasons for drop-out will be recorded as far as possible and will be analyzed in both study arms. Missing values in the ITT analysis of pure-tone audiometry are replaced by worst possible value, that means that a missing value at any follow-up visit is replaced by the respective upper limit of quantification + 10 dB.

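### Two frequency lists, ten versus five, define the same secondary comparison, and above 500 Hz the limit + 10 dB rule scores an ear with no hearing before or after surgery as zero loss

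*Protocol article*

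**What the plan says.** **Frequencies.** Among the key secondary objectives (protocol article, Methods/design) is a comparison of hearing loss between the arms at "different frequencies of pure-tone audiometry (125, 250 and 750 Hz, 1, 1.5, 2, 3, 4, 6 and 8 kHz", at months 3, 6, 9 and 12 after first fitting. Clinical outcome measures gives the corresponding secondary endpoint as "other frequencies (125 and 250 Hz, 1, 2 and 8 kHz) over time (months 3, 6, 9 and 12 post FF". Statistical analysis describes the key secondary comparison only as "in terms of residual hearing for different frequencies and different timepoints after surgery" and adds: "All analyses will be performed in line with the primary analysis using ANCOVA".

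**Scoring.** Clinical outcome measures defines the primary outcome as "hearing loss = 3 month post-FF threshold minus 1–2 days preoperative threshold". Under Data handling conventions and missing values, if there is no response at the 110 dB limit at 500 Hz, "the measurement is set to 120 dB as the upper limit of detection + 10 dB". The same section says that this "approach is used in all analyses concerning residual hearing (for all frequencies"). A missing follow-up value also receives the limit for its frequency plus 10 dB, as the worst possible value.

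**Eligibility.** Inclusion criterion 3 (Table 1) sets threshold requirements at 125, 250 and 500 Hz (85, 90 and 95 dB HL or better). It sets none at higher frequencies.

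**The concern.** The two lists describe one comparison at the same visits but disagree on its content. A reader of the results could not tell whether 750 Hz and 1.5, 3, 4 and 6 kHz were prespecified secondary endpoints, or whether leaving them out of a report departs from the plan.

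The scoring rule is a separate problem. A patient may enter the trial with no measurable hearing above 500 Hz. Loss is a difference of two thresholds and both get the same substitute value, so such an ear contributes a zero that looks like perfect preservation. These zeros enter both arms. They pull the mean loss and the treatment difference at that frequency towards zero, although those ears had no hearing there for the treatment to protect. The results would be read as the amount of hearing saved.

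**Working it through.** **1. The two lists**

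| Frequency | Objective | Endpoint |
|---|---|---|
| 125, 250 Hz | yes | yes |
| 750 Hz | yes | no |
| 1 kHz | yes | yes |
| 1.5 kHz | yes | no |
| 2 kHz | yes | yes |
| 3, 4, 6 kHz | yes | no |
| 8 kHz | yes | yes |

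The objective has 10 frequencies and the endpoint 5, and the 5 all lie within the 10. With four visits this is 10 × 4 = 40 against 5 × 4 = 20 comparisons, so 40 − 20 = 20 have an open status. The later 500 Hz comparisons (months 6, 9 and 12) agree in both places.

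**2. The scoring rule**

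The plan's own figure reproduces: 110 + 10 = 120 dB for no response at 500 Hz. Let U be the audiometer limit at another frequency; the article does not give it, but it cancels.

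- No response before and after surgery: (U + 10) − (U + 10) = 0 dB.
- No response before surgery, follow-up missing: (U + 10) − (U + 10) = 0 dB. The worst possible value becomes a loss of zero.
- For contrast, an ear at 500 Hz with a baseline of 95 dB that loses everything: 120 − 95 = 25 dB.

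The loss formula is written out for the primary outcome. I apply it to the other frequencies because the secondary analyses are to follow the primary one.

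**3. Size of the dilution**

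If a share q of ears scores 0 in both arms and the true difference in the remaining ears is d, the expected all-ear difference is (1 − q) × d. The documents do not give q, so 30, 50 and 70 % are assumed. The values d = 5 dB, mean loss 15.6 dB and SD 15.5 dB come from Sample size calculation. They are 500 Hz figures, used at higher frequencies only as an illustration.

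| q | Difference (1 − q) × 5 | Mean loss (1 − q) × 15.6 |
|---|---|---|
| 0 % | 5.0 dB | 15.6 dB |
| 30 % | 3.5 dB | 10.9 dB |
| 50 % | 2.5 dB | 7.8 dB |
| 70 % | 1.5 dB | 4.7 dB |

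The mean-loss column uses the historical mean for untreated ears.

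**4. Does power suffer?**

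I simulated 70 ears per arm with the same inputs. Further assumptions: measurable baselines uniform from 50 to 110 dB, unmeasurable baselines at 120 dB, and loss unrelated to baseline among measurable ears. There were 8,000 runs per row, with a two-sided 5 % test.

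| q | All ears, unadjusted | All ears, baseline-adjusted | Measurable ears only, baseline-adjusted |
|---|---|---|---|
| 30 % | 30 % | 33 % | 35 % |
| 50 % | 20 % | 24 % | 26 % |
| 70 % | 13 % | 16 % | 17 % |

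Under the planned type of model, all ears and measurable ears differ by about 1 to 2 points. The baseline covariate recovers most of the precision because the affected ears share one extreme baseline value. It does not remove the dilution: the baseline-adjusted all-ear estimates averaged 3.5, 2.5 and 1.5 dB.

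**The case against.** **The lists are nested, and the full protocol or analysis plan may settle the matter.** No shared frequency is treated differently, which limits the conflict to five frequencies. But the article states both lists, so this is a contradiction in its text and not a detail left to another document.

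**The zero is an honest score.** An ear with no hearing at a frequency loses none there, and an average over all randomized ears answers a legitimate intention-to-treat question. This stands as a reason to keep the all-ear analysis. It does not make that analysis a good measure of how much hearing the treatment preserves, because it cannot tell full preservation from nothing to preserve.

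**Stronger readings that the documents do not support:**

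- *The set will be chosen after the results are known.* The statisticians stay blinded until the blind data review is complete, and nothing suggests such an intention. Blinding does not, however, say which list applies.
- *Secondary error rates are out of control.* The article states a rejection rule for the primary hypothesis only and makes no success claim for secondary endpoints. A familywise error computed for 40 or 20 independent tests would not fit correlated frequencies and repeated visits in the same ear.
- *The rule costs material power.* That holds only for an unadjusted comparison. The planned baseline covariate removes most of the gap.
- *The primary result is biased in this way.* Eligibility requires 95 dB HL or better at 500 Hz against a limit of 110 dB, so a non-measurable preoperative value there should be rare.

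**Conclusion.** Both parts hold, for the secondary audiometric analyses only. The inconsistency between the lists is a matter of fact and leaves 20 comparisons without a settled status. The zero-loss score follows from reading the eligibility criteria, the loss definition and the limit + 10 dB rule together; the article does not state it outright. It applies above 500 Hz, to ears with no preoperative response and with no response or a missing value at follow-up. The harm is a treatment difference and mean loss diluted in proportion to the share of such ears. That share and the limits at other frequencies are not given, so the true size is unknown, and the figures of 3.5, 2.5 and 1.5 dB illustrate an assumed range. This should be corrected, but it does not threaten the primary conclusion.

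**What to change.** 1. State one frequency list and use it both in the key secondary objectives and under Clinical outcome measures, with a reference to it in Statistical analysis.
2. For each frequency above 500 Hz, analyse hearing loss in ears with a measurable preoperative threshold at that frequency. Report the number of excluded ears per arm.
3. Keep the all-ear analysis with the limit + 10 dB rule as a sensitivity analysis.

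The cost is some wording and one flag per frequency in the data set. The downside is fewer ears in each high-frequency analysis. Because the subset is fixed before surgery, comparability of the arms is largely kept. The preoperative test at 1–2 days can fall just after the first dose, which starts 2 days before surgery; the exclusion counts per arm would show any imbalance.

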### Inclusion and exclusion criteria

The patient must meet specific criteria during consultation with the ENT surgeon before inclusion and randomization. The appropriate examinations will be performed to make sure that the patients meet the exclusion and inclusion criteria. During the study, the patient has the right to leave the study at any time. If the patient decides to stop the intake of the study medication he may continue the study and will be further followed up.

Patients will be eligible for the trial if they fulfill all the inclusion criteria (Table 1) and none of the exclusion criteria (Table 2).

**Table 1 Tab1:** Inclusion criteria of the PROHEARING clinical trial

	Inclusion criteria
1.	18 years of age or older
2.	No or little benefit from a conventional hearing aid, defined as preoperative auditory speech understanding of less or equal 60 % in Freiburger monosyllables at 65 dB SPL, best aided in the ear to be implanted
3.	Residual hearing better or equal than 85 dB HL at 125, 90 dB HL at 250 Hz and better or equal than 95 dB HL at 500 Hz in the ear to be implanted
4.	Ability to understand the study procedures, possible risks and benefits, and to give informed consent
5.	Informed Consent Document is signed.
6.	Patients must agree not to use daily vitamin preparations containing vitamins A, C or E or magnesium during the course of the study, and beginning at least 48 hours prior to first intake of the study medication
7.	Female patients 50 years of age or older at the day of inclusion who have been postmenopausal for at least 1 year *Or* Female patients who have a negative hCG serum pregnancy test and meet one or more of the following criteria: are 6 weeks after surgical sterilization by bilateral tubal ligation or bilateral ovariectomy with or without hysterectomy are using proven oral, injected or implanted hormonal contraceptive methods: intrauterine device or intrauterine system barrier methods: condom or occlusive cap (diaphragm or cervical/vault caps) *with* spermicide (foam/gel/film/cream/suppository) male sterilization (if the absence of sperm in the ejaculate is documented. For female participants the vasectomized male partner should be the sole sexual partner for that subject) true abstinence (periodic abstinence and coitus interruptus are not acceptable methods of contraception) only female sexual partners

*hCG* human chorionic gonadotropin, *HL* hearing level, *SPL* sound pressure level

**Table 2 Tab2:** Exclusion criteria of the PROHEARING clinical trial

	Exclusion criteria
1.	Ossification or any other cochlear anomaly that might prevent complete insertion of the electrode array, as confirmed by medical examination and tests including imaging (e.g., digital volume tomography, DVT)
2.	Signs of retrocochlear or central origin to hearing impairment as confirmed by medical examination and tests including imaging (e.g., DVT)
3.	Medical or psychological conditions which contraindicate surgery (e.g., active middle ear infections, tympanic membrane perforation)
4.	Pregnancy or lactation
5.	Additional handicaps that would prevent participation in evaluations
6.	Contraindications for ACEMg: hepatopathy (transaminases or γ-GT ≥2 x upper limit of normal, ULN) severe renal insufficiency (serum creatinine >2 x ULN) disposition to kidney stones iron-storage disease (thalassemia, hemochromatosis, sideroblastic anemia) co-medication with vitamin K antagonists heavy smoking (20 cigarettes per day or more)
7	Current participation in any other clinical trial and/or participation in another clinical trial within 30 days before the study begins

*ACEMg* vitamins A, C, E and magnesium, *DVT* digital volume tomography, *ULN* upper limit of normal

### Blinding and randomization

This is a double-blind clinical trial. Patients fulfilling inclusion/exclusion criteria and giving written consent to participate in this study are randomized 1:1 to ACEMg or placebo. The randomization is stratified by the length of the electrodes (short (16 and 20 mm) versus medium (24 mm) versus long (28 mm)) as planned preoperatively (albeit the length of the electrode is finally determined during surgery). Randomization is performed centrally using a web-based randomization tool. Randomization lists are used to prepare blinded study treatments. The manufacturer provides optically identical investigational medicinal products (IMP) of ACEMg and placebo. Sealed envelopes for emergency unblinding were prepared prior to the study and handed out to the investigator. In addition to blinding patients and investigators, the trial statisticians will stay blinded until the blind data review is successfully completed.

